### Safety assessment

2.5

Throughout the study, meticulous documentation will be maintained for all AEs encountered. This documentation will include comprehensive details such as treatment group allocation, time of occurrence, duration, severity, management interventions, and outcomes. The severity of AEs will be assessed using the Common Terminology Criteria for Adverse Events (CTCAE) version 5.0 (27), published by the National Institutes of Health (NIH), with grades 3-5 classified as severe AEs. Potential AEs associated with TFM may include, but are not limited to, xerostomia, dizziness, respiratory symptoms, scalding sensations, itching, and fainting.

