### Study design

2.1

The study is designed as a prospective, single-center, open-label, parallel-group, randomized controlled clinical trial. It aims to evaluate the efficacy and safety of TFM treatment in breast cancer survivors with CRF and to preliminarily explore its potential mechanisms. The study duration is 65 days, including a 5-day screening period, a 30-day treatment period, and a 30-day follow-up period. We plan to enroll 70 participants at the Hospital of Chengdu University of Traditional Chinese Medicine, who will be randomly assigned in a 1:1 ratio to either the waitlist control (WC) group or the TFM group. During the 30-day treatment period, all patients will receive standard care. Patients in the TFM group will receive additional TFM treatment every other day, for a total of 15 sessions. The primary outcome measure is the change in the total fatigue score on the PFS at the end of treatment compared to baseline. The study flow is illustrated in **Figure 1**.

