### Interventions

2.3

All patients will receive the standard care for CRF as recommended by the Oncology Branch of the Chinese Medical Association (24). The specific regimen will include: 1) Psychological support: imparting knowledge on breast cancer recovery and CRF, and engaging in weekly therapeutic communication with the patients, each session lasting approximately 2 hours, to assist in managing adverse emotions; 2) Nutritional management: conducting a nutritional risk assessment once a week using the Nutritional Risk Screening 2002 (NRS 2002) tool, with patients identified at nutritional risk being referred to the nutritional department for specialized treatment; 3) Sleep management: overseeing the establishment and maintenance of regular sleeping schedules and environments conducive to sleep, with pharmacological treatment being administered as necessary; 4) Exercise guidance: supervising patients to partake in 180 to 300 minutes of moderate-intensity physical activities per week, such as brisk walking, yoga, and Tai Chi. During the study, the use of treatments outside the study protocol for CRF will be prohibited (e.g., stimulants or corticosteroids).

The TFM group will receive TFM therapy. The moxa sticks used for the treatment are produced by Chongqing Zhao’s Thunder-Fire Moxibustion Traditional Medicine Research Institute in China, each measuring 2.8 cm in diameter, 10.5 cm in length, and weighing 230 g. TFM will be carried out by four female acupuncturists, each with more than three years of experience in moxibustion therapy and holding a professional license. The acupoints for treatment will include CV6 (Qihai), CV4 (Guanyuan), SP6 (Sanyinjiao), and both sides ST36 (Zusanli). The acupuncturists will manipulate a lit moxa stick, moving it up and down at a vertical distance of 2-3cm from the skin over the acupoints for 30 minutes, inducing a sensation of deep tissue warmth without causing any burn pain. The treatment frequency will be every other day for 30 days, totaling 15 sessions. The WC group is scheduled to commence TFM therapy following the conclusion of the study.

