### Randomization and blinding

2.8

An independent statistician will use a variable block size randomization method with block sizes of 4, 6, and 8 to create a random sequence, ensuring a balanced 1:1 distribution between the TFM group and the WC group. The specifics of the group assignments will be noted on cards, which will then be sealed in opaque envelopes and stored by a third party. After completing the initial assessments, patients will sequentially open these envelopes in the order of their enrollment to discover their assigned group.

Given the novelty and uniqueness of TFM therapy, no placebo tool has yet been developed for TFM, making the implementation of a double-blind design challenging. Consequently, the study will be conducted as open-label, with the knowledge of group assignments transparent to both patients and acupuncturists. To minimize potential biases, those involved in evaluating outcomes, handling data, and performing statistical analysis will be kept unaware of the group allocations.

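### Adverse events have no stated common elicitation although TFM patients attend 15 extra sessions, and the AE record names the allocation that data handlers should not know

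*Protocol article*

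**What the plan says.** The Study design section puts safety beside efficacy: "It aims to evaluate the efficacy and safety of TFM treatment in breast cancer survivors with CRF". On how events enter the record, the Safety assessment section says only: "Throughout the study, meticulous documentation will be maintained for all AEs encountered". On content it says: "This documentation will include comprehensive details such as treatment group allocation, time of occurrence, duration, severity, management interventions, and outcomes". Severity is graded by CTCAE version 5.0, and the events expected with TFM include dry mouth, dizziness, respiratory symptoms, itching, scalding sensations and fainting.

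On contact, the Interventions section says of TFM: "The treatment frequency will be every other day for 30 days, totaling 15 sessions". Waitlist patients have no counterpart to these sessions. Both arms receive standard care, which includes "engaging in weekly therapeutic communication with the patients, each session lasting approximately 2 hours" and "conducting a nutritional risk assessment once a week using the Nutritional Risk Screening 2002 (NRS 2002) tool", together with sleep management and supervised exercise. Both arms complete the PFS at baseline and on days 10, 20, 30 and 60.

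On masking, the Randomization and blinding section says that patients and acupuncturists know the allocation, but that "those involved in evaluating outcomes, handling data, and performing statistical analysis will be kept unaware of the group allocations". Under Quality control and data management, paper case report forms are entered twice by two independent staff.

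**The concern.** There are two separate issues.

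**Ascertainment.** Several of the expected events are mild and non-specific and can occur in breast cancer survivors who have had no moxibustion. Whether such an event is written down depends partly on how often someone is there to hear of it. For 30 days the TFM arm meets an unmasked acupuncturist every other day, and the waitlist arm does not. Without a common way of asking, an excess of recorded events in TFM could reflect harm, more frequent observation, or both. Events not asked about during the trial cannot be recovered reliably afterwards.

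**Masking.** Allocation is the first item named for the AE documentation. Anyone who enters or analyses that record as described sees the arm, yet the masking statement covers data handling and analysis without exception. In an open-label trial with a patient-reported primary outcome, this masking is one of the few remaining controls on bias.

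**Working it through.** **The plan's own figures.** The article gives no AE rate, detection probability or between-arm AE test, so there is no safety figure to reproduce. The sample size does not bear on this point. It does reproduce: 28 per arm by the Welch calculation, and 28/0.8 = 35.

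**Contacts from day 1 to day 30, baseline excluded.**
- TFM sessions: 15, TFM arm only (Interventions).
- Weekly standard-care session: about 4 in 30 days, both arms (Interventions; the count of 4 is an assumption).
- PFS assessments on days 10, 20 and 30: 3, both arms (Primary efficacy outcome).
- TFM: 15 + 4 + 3 = 22. Waitlist: 4 + 3 = 7. Ratio 22/7 = 3.1.

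This assumes that nutrition screening takes place at the weekly session, that exercise supervision adds no contact, and that no shared contact falls on a TFM session. If every shared contact coincided with a session, the count would be 15 versus 7, a ratio of 2.1.

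**Illustration 1: detection per contact.** Suppose a persistent mild symptom is equally common in both arms and each contact picks it up independently with probability d. The chance that it is recorded after k contacts is 1 − (1 − d)^k. The values of d are assumptions.

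| d | TFM, k = 22 | Waitlist, k = 7 | Ratio |
|---|---|---|---|
| 5% | 68% | 30% | 2.2 |
| 10% | 90% | 52% | 1.7 |
| 20% | 99% | 79% | 1.26 |
| 30% | 99.96% | 92% | 1.09 |

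With 12 further shared contacts, for example supervised exercise, the counts become 34 versus 19. Then d = 5% gives 82% versus 62%, and d = 10% gives 97% versus 87%. The gap narrows but keeps its direction.

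**Illustration 2: relative detection.** Take 35 per arm, a true risk of 20% in both, full detection in TFM and 50% detection in the waitlist arm. Expected recorded counts are 35 × 0.20 = 7.0 and 35 × 0.20 × 0.5 = 3.5, an apparent risk ratio of 2.0. A two-sided 5% test (normal approximation) would show a false TFM excess with probability 21%, against 2.5% under equal detection. At 75% relative detection the figures are 1.33 and 8%. No such test is planned, so this only shows how far the descriptive table could mislead.

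**Masking, statements side by side.** Safety assessment places allocation in the AE documentation. Randomization and blinding keeps data handlers and analysts unaware of it. Quality control and data management says that the paper forms hold demographic information and assessment outcomes. It names AE reporting and case report form completion next to each other as training topics, but does not say whether AE records travel with those forms. Both masking statements can be true only if the AE record, or its allocation field, is withheld from masked staff. The article describes no such separation.

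**The case against.** This is a condensed article. It does not say that events are only volunteered, or that the arms are questioned differently, and the timeline figure or the full protocol may schedule AE questions. Waitlist patients are seen at least weekly, once for about two hours, and direct questioning there could bring detection close to complete. The ratio then falls towards 1, as the 20% and 30% rows show. Extra visits are inherent in comparing a hands-on therapy with a waiting list, and over-detection would overstate the harm of TFM, not hide it. The article plans no between-arm AE test and treats everything except the primary outcome as exploratory. Unmasked AE transcription would also do little to a fatigue score that patients rate knowing their arm.

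Most of this stands, and it rules out several stronger readings. A reader might infer that the safety comparison is biased; only exposure to bias is shown. A reader might infer that masking is broken; the article never says that masked staff receive AE records with a readable allocation. A reader might also infer that relatedness will not be recorded. The list of details is introduced as examples, the pilot was reported in terms of treatment-related events, and a condensed article may leave causality coding to the full protocol, so no finding rests on that.

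The objection does not remove the 15-session imbalance or the two unreconciled statements about allocation. Both are in the text.

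**Conclusion.** The point holds in limited form. The descriptive AE comparison, which is the trial's answer to a stated aim, is open to unequal ascertainment, probably raising recorded counts in TFM. Under the assumed contact counts the apparent ratio could lie anywhere from about 1.1 to 2.2 with no true difference. It would be 1 if detection were equal. These figures depend on assumed detection probabilities and on independence between contacts, and more shared contacts reduce them. It does not follow that the trial cannot answer its safety question. Sample size, alpha and the primary analysis are unaffected.

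The statements on allocation in the AE record and on masked data handling are inconsistent unless the AE record is kept from masked staff, and they should be reconciled. Both matters are worth correcting because the correction is cheap, not because damage has been shown.

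**What to change.** - Ask every patient in both arms the same short AE checklist (the events already listed under Safety assessment plus one open question) at the existing day 10, 20, 30 and 60 assessments. Base the between-arm comparison on those records.
- Still report all events. List separately those noted only at TFM sessions, such as scalding or fainting.
- At each visit complete the PFS before the AE checklist, since an answer such as a scald may reveal the arm to a masked evaluator.
- Leave allocation off the AE form and link it by study number after database lock. Because event content can itself reveal the arm, keep AE forms and TFM session logs apart from the outcome forms that go to masked data entry.
- State in the masking paragraph who may see AE records before lock.

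The cost is a few minutes per existing visit, one form redesign and some protocol wording, with no added visits or staff. The downside is that more mild events will be recorded in the waitlist arm.

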### Participant timeline

2.6

**Figure 2** presents a detailed timeline, illustrating the comprehensive schedule for the measurement of outcomes and the systematic collection of data.

**Figure 2 f2:**
[figure not shown]
Timeline of enrollment, intervention, and assessment milestones. HPA, hypothalamic-pituitary-adrenal; TFM, thunder-fire moxibustion.

### Sample size

2.7

The sample size was calculated based on the primary efficacy outcome, using data from a preceding pilot study. At the end of the 30-day treatment period, total fatigue scores in the TFM and WC groups decreased by 1.93 ± 0.47 and 0.94 ± 0.35 points, respectively, compared to baseline. The sample size calculation was conducted using the “Two-Sample T-Tests for Superiority by a Margin Allowing Unequal Variance” module in PASS software (version 15.0). Assuming a 20% dropout rate, a one-sided α of 0.025, a statistical power (1-β) of 0.99, and a superiority margin of 0.5, it was determined that at least 35 patients should be allocated to each group. Since the primary efficacy outcome will be analyzed using a linear mixed model, which offers greater statistical power than the traditional two-sample t-test (28), the larger sample size derived from the t-test calculation will further enhance the robustness and reliability of the analysis.

### Randomization and blinding

2.8

An independent statistician will use a variable block size randomization method with block sizes of 4, 6, and 8 to create a random sequence, ensuring a balanced 1:1 distribution between the TFM group and the WC group. The specifics of the group assignments will be noted on cards, which will then be sealed in opaque envelopes and stored by a third party. After completing the initial assessments, patients will sequentially open these envelopes in the order of their enrollment to discover their assigned group.

Given the novelty and uniqueness of TFM therapy, no placebo tool has yet been developed for TFM, making the implementation of a double-blind design challenging. Consequently, the study will be conducted as open-label, with the knowledge of group assignments transparent to both patients and acupuncturists. To minimize potential biases, those involved in evaluating outcomes, handling data, and performing statistical analysis will be kept unaware of the group allocations.

### Statistical analysis

2.9

All analyses will be conducted within the intention-to-treat population, encompassing all randomized participants. For continuous variables, data adhering to a normal distribution will be expressed as mean ± standard deviation, while non-normally distributed data will be presented using the median and interquartile range. The Shapiro-Wilk test will be used to determine the normality of the data. Categorical variables will be depicted as frequencies and percentages. The planned statistical analyses will be conducted using SPSS software (version 28.0) and the R programming language (version 4.3.1). Significance testing will be bilateral, with a P-value of ≤ 0.05 denoting statistical significance.

To compare the longitudinal trajectories of changes in PFS scores from baseline between groups at successive follow-up time points, linear mixed models will be employed. Given the correlation between repeated measures within the same participant, this model will include participant-specific random effects (29). The fixed effects of the model will include group, follow-up time, and the interaction between group and follow-up time (30). Covariates will include age and baseline PFS scores. No imputation of missing data is planned, as the analysis model itself accounts for missing data and remains valid under the missing-at-random assumption.

For other continuous outcome measures, such as KPS scores, HPA axis-related hormonal factors, and inflammatory markers, comparison between groups will employ analysis of covariance adjusting for baseline values if the data are normally distributed. If not, the Mann-Whitney U test will be applied. Missing data will be addressed through the application of the last observation carried forward method.

We plan to conduct predefined subgroup analyses for the primary outcome, considering the following baseline variables: age (≤55, >55), nutritional risk (no, yes), sleep disorder (no, yes), fatigue severity (moderate, severe), body mass index (≤24, >24), KPS score (70, 80, 90, 100), cancer stage (I, II, III), cancer subtype (Luminal A, Luminal B, HER2-positive, triple-negative), and cancer treatment (surgery, radiotherapy, chemotherapy, targeted therapy, endocrine therapy). Consequently, except for the primary outcome, the interpretations of other outcomes and subgroup analyses will be treated as exploratory.

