#### Primary efficacy outcome

2.4.1

The primary efficacy outcome is the change in the total fatigue score on the PFS at the end of a 30-day treatment period relative to baseline. The PFS is a well-validated, multidimensional tool used to assess the severity of CRF and is highly sensitive to fluctuations in fatigue levels over time (14). It has been widely utilized in clinical trials assessing CRF interventions in breast cancer survivors (25, 26) thereby enhancing the external validity and comparability of our study results. The PFS consists of 22 rating items, which are divided into four subdomain scales: behavioral fatigue (6 items), emotional fatigue (5 items), sensory fatigue (5 items), and cognitive fatigue (6 items), with each item scored on a scale from 0 to 10. The total fatigue score is the average of these 22 items, with severity categorized as mild (1-3 points), moderate (4-6 points), and severe (7-10 points). Assessments are conducted at baseline, on days 10, 20, and 30 (end of treatment), and on day 60 (end of follow-up).

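### The standard error at day 30, and the missing-at-random claim, rest on a covariance described only as participant random effects; a visit-specific covariance is a cheap, safer choice (minor)

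*Protocol article*

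**What the plan says.** Section 2.4.1 fixes a single visit as the endpoint: "The primary efficacy outcome is the change in the total fatigue score on the PFS at the end of a 30-day treatment period", compared with the starting value. The questionnaire is nevertheless completed several times: "Assessments are conducted at baseline, on days 10, 20, and 30 (end of treatment), and on day 60 (end of follow-up"). The model therefore has four post-baseline visits.

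Statistical analysis (2.9) plans a linear mixed model for change in PFS. On correlation it says: "Given the correlation between repeated measures within the same participant, this model will include participant-specific random effects". On the mean structure: "The fixed effects of the model will include group, follow-up time, and the interaction between group and follow-up time". It then names two adjustment variables: "Covariates will include age and baseline PFS scores". On missing data, imputation is declined because "the analysis model itself accounts for missing data and remains valid under the missing-at-random assumption".

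The section does not say whether the random effects are an intercept alone or an intercept and a slope. It mentions no residual structure, no visit-specific variance and no robust standard error.

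Sample size (2.7) gives the only SDs of change, both for day 30: "total fatigue scores in the TFM and WC groups decreased by 1.93 ± 0.47 and 0.94 ± 0.35 points". The sizing module is "Two-Sample T-Tests for Superiority by a Margin Allowing Unequal Variance".

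**The concern.** Random effects are a reasonable device for a trajectory, but the primary question concerns one visit. With a random intercept and one residual variance, the model assumes the same variance of change at days 10, 20, 30 and 60 and the same correlation between every pair of visits. Change scores can well be less variable early in treatment than at its end, and they can also be most variable at day 60. In the first case the standard error at day 30 is too small, and in the second it is too large.

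What is at stake is the type I error and the coverage of the confidence interval for the primary contrast. With dropout there is a second effect. Under missing-at-random, the model uses the earlier visits to make up for the missing day-30 values, and the covariance determines how. If the covariance is wrong, the estimate itself can shift. The sample size allows for 20% dropout, so this is not an empty case.

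**Working it through.** **1. The plan's own figure.** Inputs from Sample size (2.7): difference 1.93 − 0.94 = 0.99; margin 0.5; SDs 0.47 and 0.35; one-sided α 0.025; power 0.99; dropout 20%.

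- Normal approximation: (0.47² + 0.35²)(1.960 + 2.326)² / 0.49² = 26.3, so 27 per arm.
- Unequal-variance t-test: 28 per arm (power 0.9913; 27 gives 0.9892). Then 28 / 0.8 = 35.

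The stated 35 per arm is reproduced. The sizing is not in question here.

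**2. Standard error at day 30 under a random intercept and one residual variance.** Assumptions: complete data, a separate mean for each arm and visit, no covariate adjustment, large-sample reference. The fitted variance at every visit is then the mean of the four visit variances, so

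model SE / true SE = √(mean of the four visit variances / day-30 variance)

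two-sided type I error = 2 × [1 − Φ(1.96 × ratio)].

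The article gives no SD for days 10, 20 or 60, so all the patterns below are assumed. They are SDs relative to day 30 = 1.

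| Day 10 / 20 / 30 / 60 | SE ratio | Type I error |
|---|---|---|
| 1 / 1 / 1 / 1 | 1.00 | 0.050 |
| 0.8 / 0.9 / 1 / 1.1 | 0.96 | 0.061 |
| SD growing with √time | 1.00 | 0.050 |
| 0.8 / 0.9 / 1 / 1.5 | 1.08 | 0.034 |
| 0.6 / 0.8 / 1 / 1 | 0.87 | 0.090 |
| 0.4 / 0.6 / 1 / 1 | 0.79 | 0.120 |
| 0.9 / 1 / 1 / 1.8 | 1.23 | 0.016 |

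Example, second row: (0.64 + 0.81 + 1 + 1.21) / 4 = 0.915, and √0.915 = 0.96.

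**3. Allowing for measurement error.** Patterns in which the variance of change starts from zero are extreme, because measurement error in two questionnaire scores puts a floor under every visit. Take relative variances v and, as an assumption, let half the day-30 variance be a constant floor, so that v becomes 0.5 + 0.5v.

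| Relative variances v | Ratio (type I), no floor | Ratio (type I), with floor |
|---|---|---|
| 1/3, 2/3, 1, 1 | 0.87 (0.090) | 0.94 (0.067) |
| 1/9, 4/9, 1, 1 | 0.80 (0.117) | 0.91 (0.076) |
| 1/3, 2/3, 1, 2 | 1.00 (0.050) | 1.00 (0.050) |
| 1/9, 4/9, 1, 4 | 1.18 (0.021) | 1.09 (0.032) |

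**4. Intercept plus slope.** With an assumed AR(1) correlation of 0.5 to 0.85, the best-fitting random-intercept-and-slope covariance gives ratios of about 0.74 to 1.12 over similar patterns. A slope does not remove the dependence on the other visits.

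**5. Missing at random.** Large simulated sample under these assumptions: true difference 0.99, day-30 SD 0.414 (root mean square of 0.47 and 0.35), adjacent-visit correlation 0.8, and about 20% dropout in the TFM arm only, after day 20, likelier after a poor day-20 response. When the variance differs between visits, the random-intercept estimate is too high by about 0.03 to 0.05 points, or about 0.01 to 0.03 with the floor of step 3. An unstructured covariance returns 0.99 up to simulation error.

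**6. Effect on the conclusion.** At 28 completers per arm, SE = √((0.47² + 0.35²) / 28) = 0.111 and z = 0.99 / 0.111 = 8.9. With the SE inflated by 20%, z = 7.4.

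**The case against.** The strongest reply is that the article never commits to a random intercept with one residual variance. It says random effects, in the plural, and random effects can be combined with visit-specific residual variances. Residual structure, degrees of freedom and convergence rules are ordinarily left to an analysis plan, and none is shown here. This stands, and it rules out a stronger reading that a reader might infer: that the plan fixes one shared residual variance and so misstates the day-30 standard error by about 20%. The shared variance is the common default, not the article's text, and the 20% depends on assumed visit SDs that differ strongly. The direction is open too, so the article does not show an inflated false-positive rate.

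A second tempting inference is that sizing with unequal arm SDs contradicts a model with a common variance. It does not. With 28 and 28 completers the pooled and separate-variance standard errors are identical. With 25 TFM and 33 control completers the pooled one is 4% too small, with the numbers reversed 4% too large, and 28 against 35 gives a type I error of about 5.8%. Allocation is 1:1, so this matters little.

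What survives is narrower. Random effects are a stated choice, the only correlation device named, and the missing-data claim is built on that model. Neither common form of them guarantees the right variance at the one visit that matters, and a better choice is available at almost no cost.

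**Conclusion.** The point holds as a minor, conditional one. Under the usual implementation, the standard error of the primary contrast depends on the variances at days 10, 20 and 60, and the missing-at-random statement depends on the covariance being right.

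The size cannot be derived from the article. It is 0 to 4% if visit SDs are equal, rise mildly or grow with the square root of time, and about 5 to 10% under moderate growth. It reaches about 20% in either direction, with type I error roughly 2% to 12%, only under strongly different SDs. Any bias from informative dropout is a few hundredths of a point, under half of the planned standard error (0.05 / 0.111 = 0.45), and it favours treatment in the case examined.

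These figures rest on assumed visit SDs, large-sample formulas without covariates, and one dropout pattern. At the pilot effect the conclusion would be the same. The gain is a correct interval, and a sound test should the true effect be much smaller than in the pilot.

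**What to change.** Replace the sentence on random effects with a full statement of the primary model: a REML mixed model for repeated measures with visit as a categorical factor, group, group by visit, age and baseline PFS. Use an unstructured covariance over days 10, 20, 30 and 60, common to both arms, and Kenward-Roger degrees of freedom. Name a heterogeneous Toeplitz covariance as the fallback if the model does not converge. State that the primary result is the day-30 group contrast from this model.

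A covariance that differs by arm can be added as a sensitivity analysis, but it is not needed for the primary model.

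The cost is one or two sentences and 10 covariance parameters against up to 70 × 4 = 280 observations, which means a slight loss of degrees of freedom. No change to sample size, visits or data collection is needed.

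### The primary mixed model, as listed, gives baseline fatigue one common slope over four visits while the primary contrast is day 30 alone; a baseline-by-time term would be a cheap safeguard

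*Protocol article*

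**What the plan says.** Section 2.4.1 fixes a single-visit primary endpoint: "The primary efficacy outcome is the change in the total fatigue score on the PFS at the end of a 30-day treatment period". The scale is also administered at days 10, 20 and 60, and section 2.9 puts the post-baseline changes into one linear mixed model with random effects for each participant.

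The mean structure is given term by term: "The fixed effects of the model will include group, follow-up time, and the interaction between group and follow-up time". The next sentence adds "Covariates will include age and baseline PFS scores". No interaction of baseline with time is listed. The structure of the random effects is not given.

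Missing PFS scores are not imputed, because the model is said to be one that "remains valid under the missing-at-random assumption".

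**The concern.** With only group crossed with time, the regression of change on baseline is forced to be the same at day 10, at the end of treatment (day 30) and 30 days after treatment (day 60). The day-30 group difference is then corrected for chance baseline imbalance with a pooled slope instead of the day-30 slope.

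If the two differ, two things follow.

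- **Precision.** Part of the baseline imbalance stays in the day-30 estimate as extra noise. Section 2.8 describes blocked randomisation without strata, so some imbalance in baseline fatigue is to be expected.
- **Missing data.** Validity of a likelihood analysis under missing at random needs a correct model for the mean. If patients with high or low baseline fatigue drop out at different rates in the two arms, those still observed at day 30 differ in baseline. Correcting that difference with the wrong slope leaves an error that does not average out over randomisations. The trial is open-label, plans for 20% dropout and asks only one arm to attend 15 sessions, so such a pattern is possible.

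**Working it through.** **1. The plan's own figure.** Inputs from section 2.7: mean decreases 1.93 (SD 0.47) and 0.94 (SD 0.35), margin 0.5, one-sided α 0.025, power 0.99, dropout 20%.

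- Effective difference: 1.93 − 0.94 − 0.5 = 0.49.
- An unequal-variance t-test (noncentral t) gives power 0.9892 at 27 per arm and 0.9913 at 28.
- 28 / (1 − 0.20) = 35 per arm, as stated.

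This calculation uses no covariate, so the point below cannot change it.

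**2. Precision with complete data.** The documents give no baseline SD, no correlation of baseline with change and no slopes by visit, so what follows is assumed. With a random intercept and complete data, the common slope is the simple mean of the four visit slopes, day 30 included. Let r be the within-arm correlation of baseline with day-30 change, and m the mean slope as a fraction of the day-30 slope. In standardised units the gap between the day-30 and the mean slope is g = (1 − m)r, and

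excess variance of the day-30 contrast = g² / (1 − r²) = (1 − m)² r² / (1 − r²).

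Two assumed profiles of the slopes at days 10, 20, 30 and 60, relative to day 30:

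| Profile | m | r = 0.3 | r = 0.5 | r = 0.6 | r = 0.7 |
|---|---|---|---|---|---|
| steep: 1/3, 2/3, 1, 0.8 | 0.70 | 0.9% | 3.0% | 5.1% | 8.7% |
| flatter: 0.6, 0.8, 1, 1 | 0.85 | 0.2% | 0.8% | 1.3% | 2.2% |

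Example: steep profile, r = 0.5: 0.30² × 0.25 / 0.75 = 0.030.

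**3. Simulation of the same quantity** (28 per arm, 20,000 replicates, residual correlation between visits 0.5). Standard error of the day-30 difference:

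| Standardised slopes, days 10, 20, 30, 60 | Unadjusted | Common slope | Visit-specific slopes | Common / specific |
|---|---|---|---|---|
| −0.3 at all visits | 0.1107 | 0.1064 | 0.1068 | 0.996 |
| −0.1, −0.2, −0.3, −0.2 | 0.1107 | 0.1068 | 0.1065 | 1.003 |
| −0.1, −0.3, −0.5, −0.3 | 0.1104 | 0.0987 | 0.0963 | 1.025 |
| 0, −0.3, −0.6, −0.3 | 0.1107 | 0.0952 | 0.0893 | 1.065 |

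The last row is deliberately extreme: it assumes that change at day 10 does not depend on baseline at all. No bias appeared in any row. The common slope beat no adjustment in every row, and with equal slopes it is very slightly the better choice.

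**4. Power.** At 28 per arm and r = 0.5, power against the 0.5 margin is 0.9989 with visit-specific slopes, and 0.9983 (g = 0.2) or 0.9973 (g = 0.3) with a common slope. Against zero it is about 1.000 throughout.

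**5. Dropout related to baseline.** Assumed: 35 per arm, residual correlation 0.5, no true effect, the steep profile with r = 0.5, and about 20% dropout after day 20.

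- Dropout depends on baseline in the control arm only: common-slope bias about 0.06 SD.
- It depends on baseline in opposite directions in the two arms: about 0.11 SD.
- With the baseline-by-time term: about 0.01 SD in both cases, within simulation error.

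Across repeated checks the common-slope bias lay between about 0.04 and 0.13 SD. With the pilot's pooled SD, √[(0.47² + 0.35²)/2] = 0.414, that is 0.04 × 0.414 = 0.017 to 0.13 × 0.414 = 0.054 points, against an expected difference of 0.99.

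**The case against.** The strongest reply is that a common baseline slope is a legitimate specification, that an article often leaves covariate-by-time coding to the analysis plan, and that the text does not forbid the interaction. That stands in part: nothing here is contradictory, and a fuller plan may already contain the term. But section 2.9 does list the model's terms and gives a time interaction to group only, so the formula as stated can be commented on.

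A second reply is that nothing in the documents shows the slopes to differ. That stands. Error and transient variation in the baseline score enter every change score equally from day 10 on, and entry requires a PFS score of at least 4, so regression to the mean should already be visible at the first visit. Both favour the flatter profile and the small end of the range.

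Three stronger readings are tempting and are not supported:

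- **That precision is certainly lost, or that the interaction is free.** With equal slopes nothing is lost, and the interaction costs about 0.4% of the standard error.
- **That the covariate is the only correction for baseline imbalance.** The response is already change from baseline; the covariate refines that subtraction.
- **That the power argument in section 2.7 fails.** That section compares the mixed model with an unadjusted t-test, and the common-slope model beat the unadjusted analysis in every simulated scenario.

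**Conclusion.** The point holds as a minor, conditional improvement. As listed, the day-30 contrast is adjusted with a baseline slope pooled over all four visits, and the article gives no reason for that constraint.

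The cost in precision is about 0.2% to 9% of variance for the two assumed profiles with r from 0.3 to 0.7, and zero if the slopes are equal. The upper end needs both the steep profile and r = 0.7. These figures also rest on a random intercept and complete data.

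The modest bias needs two conditions together: slopes that differ by visit, and dropout that depends on baseline differently by arm. If both hold, the reliance on missing at random is weaker than stated, because the mean model is then misspecified.

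The 35 per arm and the 0.99 power do not depend on any of this, and no error in a stated figure is alleged.

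**What to change.** In section 2.9, add the baseline PFS by follow-up time interaction to the fixed effects, with time as a factor. Do so for the total score, and for each subdomain model using that subdomain's own baseline score. The day-30 group difference is then adjusted with the day-30 slope. If the full analysis plan already has this term, the article's list of terms only needs to match it.

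The cost is one phrase and three extra parameters per model (four visit slopes in place of one), with no new data. If the slopes turn out equal, the standard error with complete data is about 0.4% larger (0.1068 / 0.1064 = 1.004).
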